**Epidural Morphine in COVID ARDS patients with a high respiratory drive: a double-blind, randomized controlled trial**

**Introduction**

COVID-19 ARDS (CARDS) is associated with a high respiratory drive. (1) If the high respiratory drives are not reduced by oxygen administration and optimal noninvasive support, persistently strong spontaneous inspiratory efforts simultaneously increase tissue stresses and raise pulmonary transvascular pressures, vascular flows, and fluid leakage (i.e., P-SILI). (2) Progressive deterioration of lung function (a VILI vortex) may then rapidly ensue. The adverse effects of high respiratory drive: fatigue, lung strain, and patient self-induced lung injury P –SILI, when patients are left unintubated, are well known. (3)

The only armamentarium available to the clinician at the bedside to reduce abnormally high respiratory drive is to deeply sedate and paralyze the patient and initiate 'lung-protective ventilation. (1) Partial paralysis after intubation has been attempted to reduce high respiratory drives during weaning from ventilation. (4) Literature is replete with studies highlighting the negative consequences of intubation, mechanical ventilation, sedation, and neuromuscular blockers. (5) Infectious complications of intubation are more significant in these patients. (6) The COVID19 ARDS patient requires much higher doses of sedatives than ARDS of other etiology. (7) An association has been noted between deep sedation, coma, and increased mortality among mechanically ventilated COVID 19 patients. (8)

Opioids reduce dyspnea by altering perception, reducing anxiety, and reducing respiratory drive by acting on respiratory centers in the medulla, alleviating the mismatch between the motor drive and pulmonary afferent feedback. (9) Although considered an adverse effect of systemic and central neuraxial opioids, this property of morphine has been utilized to treat patients with both acute and chronically high respiratory drives. (10,11) Epidural morphine is known to reduce respiratory drive at much lower doses than systemic opioids and has the benefit of fewer side effects (nausea, vomiting, pruritus, and constipation) than intrathecal administration. (12,13)

Respiratory drive assessments by Diaphragmatic pressure-time product per breath (PTP_di_) from oesophageal and gastric pressure recordings or electrical activity of the diaphragm (EAdi) are not available readily to the clinician at the bedside. Although airway occlusion pressures (p0.1) have been studied as a surrogate for a high respiratory drive, (14) PTPdi and EAdi correlate well with diaphragmatic thickening fraction index TFdi (15,16), are easily available at the bedside and have been seen to have good repeatability. (17) Values below or beyond 15-30% have been associated with delayed weaning and hyperinflation of the lung.(18,19)

We have previously initiated a feasibility study to look at the effect of epidural morphine to control high respiratory drive in ventilated patients (CTRI/2021/05/033509). Finding encouraging results in decreasing the drive as assessed by TFdi, while maintaining patient alertness and subjective comfort without serious adverse effects, we seek to study its effect in non-invasively ventilated COVID-19 patients.

The aim is to study the effect of epidural morphine to reduce high respiratory drive in COVID 19 patients on NIV (primary endpoint) and to study its effect on ventilator parameters, subjective patient comfort, rates of endotracheal intubation, duration of mechanical ventilation, and mortality.

**Overview of the trial (Fig. 1)**

*Design*

Parallel group, randomized, double-blind, single-center placebo control trial.

**The research question**

Aim To compare the TFDi (primary endpoint), ventilator parameters, subjective comfort, rate of intubation, length of mechanical ventilation, length of ICU stay, and mortality of moderate to severe COVID 19 patients on noninvasive ventilation (NIV), with and without epidural morphine.

*Objectives*

To compare-

Thickening Fraction index of diaphragm TFdi, surrogate for the respiratory drive (primary outcome measure)

P0.1, mechanical ventilation (MV), respiratory rate (RR), Tidal volume (Vt), subjective comfort, the dose of sedatives needed, Visual Assessment of Pain (VAS), Richmond Agitation and Sedation Scores (RASS), time to intubation, length of mechanical ventilation, the incidence of VAP, incidence of sepsis, COVID 19 markers, length of stay in ICU, length of stay in hospital and mortality between the two groups.

**Trial population**

Trial site(s) and population(s)- COVID ICU patients in AIIMS Bhubaneswar

Inclusion and exclusion criteria- Include- Adult patients with COVID 19 pneumonia 18-80 years of age. Requiring NIV to maintain oxygenation.

Exclusion criteria- Metabolic acidosis HCO3-< 16 or pH < 7.2. Severe hypoxemia warranting cessation of NIV and intubation, non-acceptance of NIV. Chronic opioid user. Uncontrolled sepsis, end of life (EOL) orders.

Sources or methods of recruitment- Daily discussion at 8 am of new admissions to COVID ICU on NIV – assessment for high respiratory drive despite Spo2 > 90 and adequate NIV support

Information for participants- PIS will be provided. Written informed consent will be taken for the patient/ kin of all eligible patients.

**Allocation of interventions**

Methods for randomization and stratification- The study research assistant will keep a central random numbers list. She will randomize according to the list available.

Methods for concealment of allocation- An opaque sealed envelope concealing the allotted randomization code will be dispatched to the ICU team.

**The interventions**

A baseline assessment of all outcome measures as appropriate will be made. Normal body temperature, RASS of -1 or 0, and VAS < 4 will be ensured by administering Midazolam ( titrated to effect) or Paracetamol as warranted.

All patients will be turned lateral or sitting position, and an injection of LA be given at L2-3 or L3-4 space. An epidural catheter will be inserted under all asepsis and fixed to the skin in the intervention group. It will be fixed firmly with antimicrobial incise drapes covering at least the lower one-third of the back. For patients who appear fidgety, catheter tunneling may also be used.

The control group will have a sham catheter fixed precisely like the intervention group but not entering the epidural space. The fixation and dressing will be similar to the intervention group.

The intervention group will be administered Injection Morphine Sulphate once every 18-24 hours into the epidural space. The doses will be escalated daily (5-10mg), titrated to the effect: escalation limited by hypoventilation resulting in respiratory acidosis (pH <7.2).

The intervention will continue for a minimum of 2 doses and a maximum of 4 doses (96 hours) of morphine. It will be stopped at 120 hours, or if: the epidural catheter gets dislodged before the second dose, the patient is weaned off noninvasive ventilation to high flow mask for a continuous period of 12 hours or requires endotracheal intubation.

The patient will be followed up till death or 28 days after ICU discharge.

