**Outcome assessment**

*Outcome measures*

TFdi, p0.1, MV, RR, Vt (average of 3 readings, ^eighth^ hourly )

Arterial blood gas and associated values-Pa o2, PaCO2, pH, HCO3, p/F ratio (at least once a day)

Spo2, Fio2, ROX index, Subjective comfort and dyspnea scores – 8^th^ Hourly

VAS, RASS, Weaning (hours off NIV on high flow mask or face mask)- (mean values over 24 hours)

Intubation- Yes/ No: Days after randomization

Length of stay in ICU

Outcome at 28 days of admission

Incidence of excessive respiratory depression (PaCO2> 45 and pH < 7.2)

Incidence of difficult/ failed epidural insertion, catheter pullouts, and complications such as bleeding/ infection/ hematoma will be documented.

Timing of outcome assessment- - Every 8^th^-hour assessment / daily / one time as detailed above

Blinding- The assessor, patient, nurses, physicians, and treating team will be blind to group allocation. One member of the team not involved in research will administer the drug.

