**Safety monitoring and adverse events**

Data and safety monitoring- Adverse effects will be documented and reported to the IEC.

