**Sample size**

Sample size justification A pilot study showed the mean TFDi in COVID 19 patients on PEEP 5 to be 45%(SD 15); To decrease mean fractional thickening of the diaphragm index by 30% after the dose of morphine with allocation in a 1:1 ratio, 21 patients will be needed in each group. Accounting for dropouts/ loss of data, 25 patients will be recruited in each limb.

*Statistical analysis*

Interim analyses are planned at 50% of sample recruitment, without unblinding to ensure that subjects are not being exposed to an unacceptable level of risk, whether the trial can be stopped early, check some of the assumptions that went into the original design and sample-size calculations of the trial (like within-group variability, recruitment rates, base event rates). The alpha spending strategy used will be one-fifth of the available 5 percent alpha at the interim analysis. i.e., the interim analysis p-value must be < 0.01 to stop the trial early and claim efficacy. Spend the remaining four-fifths of the 5 percent alpha at the end, or the end analysis p-value must be < 0.04 to claim efficacy. The two groups shall be compared for the mean TFdi (overall and 24^th^ hrly) by unpaired t-tests. Within-group comparison of TFdi shall be made (overall and 24^th^ hrly) by Repeated measures analyses.

Secondary outcomes- Intubation, Mortality, duration of mechanical ventilation, ICU stay, Subjective scores, Demographics, and severity of illness shall be compared by chi-square, t-tests, or nonparametric tests as suitable.

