**Reassess Minute volume after 30 minutes.**

- Exclusion: PaCO2 ≥ 45 mmHg *and* pH < 7.2; Compensated respiratory acidosis was accepted up to a pH 7.2 according to standard ARDS lung-protective ventilation guidelines *if GCS >12*

Compensated metabolic acidosis with HCO3 < 16mmol/l with sepsis/ acute or chronic renal failure,

Hemodynamic instability (MAP< 65 mmHg) *and* need of increasing doses of vasopressors in last 6 hrs.; GCS <12;

Contraindication to noninvasive ventilation;

Urgent need for intubation (evaluated by the clinician in charge)

Refusal to participate or participate in another study.

Do-not-intubate decision

Epidural catheter block/ dislodged/ less than two doses of the drug could be administered.

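### No rule withholds a repeat dose at the protocol's own respiratory-depression threshold, and an exclusion for fewer than two doses conflicts with intention-to-treat

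*Protocol*

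**What the plan says.** Protocol, *The interventions*: morphine is given epidurally every 18-24 hours and escalated daily within 5-10 mg, with "escalation limited by hypoventilation resulting in respiratory acidosis (pH <7.2" as the brake. Then: "The intervention will continue for a minimum of 2 doses and a maximum of 4 doses (96 hours) of morphine". Dosing stops at 120 hours, if the catheter dislodges before the second dose, after 12 continuous hours off NIV, or if intubation is required.

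*Outcome assessment* lists as an outcome "Incidence of excessive respiratory depression (PaCO2> 45 and pH < 7.2". Blood gases are due at least daily. *Demographic & ICU admission data* puts the first post-randomization gas at 12 to 24 hours, with at least one every 24 hours after that.

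The exclusion list in *Detailed methodology, with definitions* (under *Reassess Minute volume after 30 minutes*) bars patients with PaCO2 ≥ 45 mmHg and pH < 7.2, and adds: "Compensated respiratory acidosis was accepted up to a pH 7.2 according to standard ARDS lung-protective ventilation guidelines". The same list ends with an item covering a blocked or dislodged catheter and the case where fewer than two doses could be given.

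Under *Compliance and missing data*, in the second *Sample size* section, all analyses are by intention-to-treat on the groups as randomized, with a per-protocol analysis in addition.

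*Safety monitoring and adverse events* says "Adverse effects will be documented and reported to the IEC". The interim look is made "without unblinding to ensure that subjects are not being exposed to an unacceptable level of risk".

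**The concern.** There are two linked defects.

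First, limiting escalation is not the same as withholding a dose. A patient who is acidotic and hypercapnic after dose 1 is not escalated, but no visible rule says that the current dose is not repeated. The protocol counts this state as a harm and treats essentially the same state as a reason not to enrol, yet gives no instruction for a patient already in the trial.

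Second, the number of doses received is a post-randomization event, so it cannot be an eligibility criterion. If it is applied as one, patients leave the analysis because of their early course. That affects intubation, mortality and respiratory depression as outcomes, and it contradicts the rule that everyone is analysed as randomized.

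**Working it through.** **1. The plan's own figure.** The only related number is the sample size. The target difference is 45 × 0.30 = 13.5 points, and 13.5/15 = 0.9 SD. Assuming two-sided 5% and 80% power (neither power nor sidedness is stated), the t-based calculation gives 21 per group, as the protocol says. "Accounting for dropouts/ loss of data, 25 patients will be recruited in each limb" leaves 25 − 21 = 4 spare per arm. The point does not turn on this figure.

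**2. A patient with PaCO2 > 45 and pH < 7.2 after dose 1, followed through the text.**

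| Text | Does it withhold dose 2? |
|---|---|
| Escalation limit, pH < 7.2 | No; it caps the increase only |
| Stop at 120 hours, or dislodgement before dose 2 | Unrelated to this state |
| Stop after 12 hours off NIV | Unlikely; *Weaning NIV settings* asks for pH ≥ 7.35 |
| Stop if intubation is required | Only indirectly (see below) |
| Adverse-effect reporting | No; documents and reports |
| Interim analysis | No; trial level, at 50% recruitment |
| Entry exclusion, PaCO2 ≥ 45 and pH < 7.2 | No; applies at entry |

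*Criteria for endotracheal intubation* has no PaCO2 or pH trigger. Its rate criterion is RR > 40, the opposite of opioid hypoventilation. GCS < 12, or SpO2 below 85% for more than 5 minutes at FiO2 100%, could catch this patient, but only after further deterioration.

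**3. Would a current gas be available before each redose?** Assumptions: dose 1 at randomization; doses at 0, d, 2d and 3d hours with d = 18 to 24; gases at t, t+24 and t+48 with t = 12 to 24; no extra clinical gases; a gas at the dose time counts as before that dose. Redose k is covered if a gas falls after (k−1)d and no later than kd.

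All three redoses are covered only if t + 48 ≤ 3d, that is t ≤ 3d − 48. Otherwise two gases fall in the three intervals and exactly one redose is uncovered.

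- d = 18: needs t ≤ 6, impossible; always 1 of 3 uncovered. With t = 12 the gases are at 12, 36 and 60 h, and the 54 h redose has none. With t = 20 they are at 20, 44 and 68 h, and the 18 h redose has none.
- d = 19: needs t ≤ 9, impossible; always 1 of 3.
- d = 20: only t = 12 covers all three.
- d = 22: covered if t ≤ 18.
- d = 24: covered for every t up to 24; none uncovered.

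So a gas check before redosing adds at most one gas per patient, and none at 24-hourly dosing.

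**4. The two-dose item beside the analysis rule.** *The interventions* lets dosing stop before dose 2 for dislodgement, intubation or weaning. Each such patient has had fewer than two doses and meets the exclusion. *Compliance and missing data* keeps the same patients. Both cannot be applied.

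**5. Precision or selection?** With 25 per arm, t-test power for 13.5 points is 0.877 at two-sided 0.05 and 0.855 at 0.04. If all four spare patients were lost from the morphine arm (25 against 21), it is 0.845 and 0.819. The loss of power is small. The problem is that patients are removed on the basis of what happened after randomization.

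**The case against.** **The dosing is meant to respond to the patient.** It is titrated to effect with hypoventilation as the limit, NIV settings are adjusted for PCO2, and intubation stops it. This stands as evidence of intent and as partial cover, so it would be wrong to say that nothing could stop such a patient. It does not supply a rule for repeating the dose.

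**A reader might infer that blinding leaves nobody able to hold a dose**, since "The assessor, patient, nurses, physicians, and treating team will be blind to group allocation". The documents do not support that. The next sentence gives the injection to a team member not involved in the research, and that person could withhold it. Blinded clinicians can also object on clinical grounds. What is missing is the instruction.

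**A reader might infer that the two-dose minimum obliges a second dose.** The stop list that follows it includes events that can occur before dose 2, so the minimum yields. It only needs a sentence saying that it also yields to a safety hold.

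**The exclusion may be meant for technical failure or for the per-protocol set.** Its place beside catheter block and dislodgement suggests this, and it is probably the sensible intention. But it stands under exclusions and says neither.

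**The two defects seem to pull against each other**, because without a hold rule the protocol creates no safety stop after one dose. That is fair, and for this reason no figure is offered for how far the exclusion would lower the respiratory-depression rate; any such figure would rest on invented counts. The conflict does not need a safety stop: early intubation and weaning already produce it.

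**Conclusion.** Both points hold on the visible text; the study-flow figure is not shown, so a hold rule there cannot be ruled out.

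*The interventions* limits escalation but has no explicit rule to withhold a repeat dose at the protocol's own harm threshold. Followed literally, it leaves the patient scheduled for another dose in a state that would essentially have barred entry. How often this would occur is unknown, because the documents give no event rate. The only size that can be given is the sampling gap: under minimum sampling and the timing assumptions above, one of three redoses lacks a new gas at intervals from 18 to just under 20 hours, none or one from 20 to under 24, and none at 24. Since daily gases are a floor in an ICU, the real gap may be smaller.

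The two-dose exclusion contradicts the intention-to-treat rule. Its direction of bias cannot be settled from the documents, since it would remove early intubations and early weaning alike. It should be fixed before analysis; it is not evidence that the primary comparison is invalid, because the intention-to-treat statement, if it governs, keeps these patients.

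**What to change.** Make the two changes together, since a hold rule will itself produce some patients with fewer than two doses.

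1. In *The interventions*, add: the next injection (morphine or sham) is withheld while PaCO2 > 45 and pH < 7.2, regardless of the two-dose minimum; a blood gas taken since the previous dose is checked before each redose. The check is made identically in both arms, so that a hold does not reveal allocation, and the decision is passed to the administrator described under *Outcome assessment*. Clinicians should confirm the threshold and set the restart rule.
2. Remove the catheter-failure and two-dose item from the exclusion list. State under *Compliance and missing data* that all randomized patients stay in the intention-to-treat and safety analyses, and that the item defines only the per-protocol set.

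Cost: two or three sentences and, under minimum sampling, at most one extra gas per patient. Some patients will receive fewer doses, which may slightly dilute the TFdi contrast; by how much cannot be estimated from the documents.

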**Post-recruitment retention strategies**

Participant retention- Follow-up will be till stay in the hospital or 28 days, whichever is longer.

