**Intubation and mortality rates,**

Duration of NIV and invasive mechanical ventilation

Cause for conversion to IMV- Progressive respiratory failure/ New Sepsis/ Neurologic dysfunction/ Hemodynamic instability

The length of ICU-stay,

The organ dysfunctions and adverse events, including cardiac dysrhythmia, septic shock, and cardiac arrest, will be recorded until the ICU stay.

Mortality will be followed today 28.

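### Mortality has no single 28-day window, and ventilation time and ICU stay are compared with no rule for deaths

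*Protocol*

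**What the plan says.** Two places in the protocol give a time point for outcome or death:

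- Outcome assessment lists "Outcome at 28 days of admission". It does not say whether admission is to the ICU or to the hospital.
- The section on intubation and mortality rates says "Mortality will be followed today 28", read here as day 28. It gives no starting point.

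Two others set how long patients are followed:

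- The interventions: "The patient will be followed up till death or 28 days after ICU discharge".
- Post-recruitment retention strategies: "Follow-up will be till stay in the hospital or 28 days, whichever is longer". The 28 days here have no stated origin.

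The one outcome dated from randomisation is intubation: "Intubation- Yes/ No: Days after randomization".

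On analysis, the Statistical analysis text under Sample size covers the secondary outcomes in one sentence: "Intubation, Mortality, duration of mechanical ventilation, ICU stay, Subjective scores, Demographics, and severity of illness shall be compared by chi-square, t-tests, or nonparametric tests", chosen as suitable. The durations are listed plainly, as length of ICU stay and as "Duration of NIV and invasive mechanical ventilation". No text says how a patient who dies in the ICU or on the ventilator enters them.

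**The concern.** There are two separate problems.

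**The window.** A mortality comparison needs the same period of risk for every patient, starting where the arms become comparable, which is randomisation. Here the origin is admission of an unspecified kind in one place and absent in another. The two follow-up statements end at different times, and both ends move with length of stay, itself an outcome. If deaths were simply counted over follow-up, patients would be observed for unequal times, and the same late death could be in or out depending on the section used.

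**The durations.** A short stay is good when it ends in discharge and bad when it ends in death. A plain t-test or rank test on length of stay does not separate the two. If one arm has more early deaths, its mean stay is pulled down and it can look better for that reason.

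**Working it through.** The protocol gives no figure for mortality, ICU stay or ventilation time, so there is nothing of its own to reproduce on this point. The only input taken from it is 25 patients per arm; every other input below is an assumption.

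**1. Clocks.** Assumed patient: admitted day 0, randomised day 2, leaves ICU day 14, leaves hospital day 20.

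| Section | Rule | Ends on day |
|---|---|---|
| The interventions | ICU discharge + 28 | 14 + 28 = 42 |
| Outcome assessment | admission + 28 | 0 + 28 = 28 |
| Retention strategies | longer of hospital stay and 28 days | max(20, 28) = 28 from admission, or max(20, 2 + 28) = 30 from randomisation |
| Intubation and mortality rates | day 28, no origin | 28 or 30 |

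A death on day 29 falls inside the first window and outside the second. Under the last two it falls inside only if the 28 days start at randomisation.

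The two follow-up lengths can differ in either direction. The patient above has 42 against 28 or 30. One who leaves the ICU on day 10 and the hospital on day 45 has 10 + 28 = 38 against 45.

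Patients are recruited in the ICU, so ICU discharge comes after randomisation. The rule in The interventions therefore always reaches day 28 after randomisation in survivors. The retention rule need not: counted from admission, it can stop at day 28 − 2 = 26 after randomisation for a patient already discharged.

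**2. Durations.** Let m be mortality, S the mean stay of survivors and D the mean time to death in the ICU, the same in both arms, counted from randomisation and capped at 28 days.

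- Raw mean stay = (1 − m)S + mD
- Mean ICU-free days to day 28, death scored 0 = (1 − m)(28 − S)
- Raw difference, higher-mortality minus lower-mortality arm = (m_high − m_low)(D − S)

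The last line gives the condition: the higher-mortality arm shows the shorter stay only when m_high > m_low and D < S.

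For gamma-distributed stays of shape 2 and mean μ, the mean after capping at 28 is μ − (μ + 28)e^(−56/μ). This turns 12 into 11.62, 7 into 6.99, 10 into 9.86 and 14 into 13.23. For the first row below, 0.5 × 11.62 + 0.5 × 6.99 = 9.3, and 0.7 × 11.62 + 0.3 × 6.99 = 10.2. ICU-free days are 0.5 × (28 − 11.62) = 8.2 and 0.7 × (28 − 11.62) = 11.5.

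| Mortality | Survivors / deaths, mean days before cap | Raw stay | ICU-free days |
|---|---|---|---|
| 50% v 30% | 12 / 7 | 9.3 v 10.2 | 8.2 v 11.5 |
| 50% v 30% | 12 / 10 | 10.7 v 11.1 | 8.2 v 11.5 |
| 50% v 30% | 10 / 14 | 11.5 v 10.9 | 9.1 v 12.7 |
| 40% v 40% | 12 / 7 | 9.8 v 9.8 | 9.8 v 9.8 |

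For the first row, 4,000 simulated trials of 25 per arm gave 9.3 v 10.2 raw and 8.2 v 11.4 ICU-free days, agreeing with the formula within simulation error. A rank test at 5% rejected in about 7% of trials on raw stay and 21% on ICU-free days.

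**3. A less favourable case.** With survivors at 16 days, deaths at 7, mortality 30% v 50% and a t-test (5,000 simulated trials), the lower-mortality arm had the longer raw mean stay in 75% of trials. It was significantly longer in 10.5% and significantly shorter in 0.4%. With 40% mortality in both arms the figures were 50%, 2.5% and 2.3%: no bias.

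**The case against.** A reader might infer that the protocol has four contradictory mortality endpoints. It does not. The interventions and retention sections say how long patients are followed; neither names mortality as an outcome at that time. Following patients beyond an endpoint is no contradiction, and the two texts that do give a time point agree if both count from admission. Day-28 status is usually recoverable. What stands is narrower: those two texts share no stated origin, and the two follow-up lengths disagree.

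Nor do the documents say that no clock starts at randomisation. Two of the four give no origin, so randomisation is simply not stated.

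On the durations, the sentence allows any suitable nonparametric test, and one that ranks deaths worst would fit it. Handling of deaths is often left to a statistical analysis plan, which may exist. Silence alone would therefore be no finding. What remains is that the protocol itself assigns t-tests and similar tests to plainly listed durations. Followed as written, that lets an early death count as a short stay.

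A reader might also infer that the 28-day mortality result can point the wrong way, or that raw durations must mislead. Neither follows. No text ties the durations to day 28, the reversal does not touch mortality, and it needs both conditions shown above. Even in the first scenario the raw comparison is rarely significant: 7% is little above the nominal 5%.

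**Conclusion.** The concern holds in limited form. The mortality window is not fixed and the two follow-up lengths contradict each other; both follow from the text without assumptions. How many deaths would change category cannot be said from the documents, since that depends on deaths falling between the competing end dates.

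The duration problem is conditional. If mortality differs and deaths come earlier than survivors' discharge, raw ICU stay can favour the arm with more deaths by about 0.9 days (10.2 − 9.3) in the first scenario, while ICU-free days favour the other arm by about 3.3 (11.5 − 8.2). With deaths at 10 days the raw gap shrinks to 0.4; with deaths at 14 days and survivors at 10 there is no reversal; with equal mortality there is no bias. All these sizes rest on assumed mortality and stay.

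Only secondary outcomes are affected. The primary comparison of diaphragm thickening fraction and its sample size are untouched. This should be corrected, but it does not threaten the trial's main result.

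**What to change.** 1. In Outcome assessment and in the section on intubation and mortality rates, define mortality as death by day 28 after randomisation, for every patient.
2. Reconcile The interventions and Post-recruitment retention strategies to one follow-up length that covers that day. Longer follow-up may stay as descriptive information.
3. In Statistical analysis, compare ventilator-free and ICU-free days to day 28 after randomisation, scoring 0 for patients who die by then, with a rank test. Say whether time on NIV counts as ventilation, since both kinds are recorded.
4. Give raw durations descriptively, for example separately for survivors and deaths.

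Treating death as a competing event for time to intubation is a reasonable option but is not needed to settle this point.

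The cost is small: wording, and a day-28 status check for discharged patients within the follow-up that The interventions already promises. The drawback is that free days mix death with duration, so a difference may come from either and must be read beside the mortality result.
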